# A dissonance-based intervention for women post roux-en-Y gastric bypass surgery aiming at improving quality of life and physical activity 24 months after surgery: study protocol for a randomized controlled trial

**DOI:** 10.1186/s12893-018-0358-7

**Published:** 2018-05-09

**Keywords:** Bariatric surgery, Roux-en-Y gastric bypass, Dissonance-based, Intervention, RCT, Quality of life, Physical activity

## Abstract

**Background:**

Roux-en-Y gastric bypass (RYGB) surgery is the most common bariatric procedure in Sweden and results in substantial weight loss. Approximately one year post-surgery weight regain for these patient are common, followed by a decrease in health related quality of life (HRQoL) and physical activity (PA). Our aim is to investigate the effects of a dissonance-based intervention on HRQoL, PA and other health-related behaviors in female RYGB patients 24 months after surgery. We are not aware of any previous RCT that has investigated the effects of a similar intervention targeting health behaviors after RYGB.

**Methods:**

The ongoing RCT, the “WELL-GBP”-trial (wellbeing after gastric bypass), is a dissonance-based intervention for female RYGB patients conducted at five hospitals in Sweden. The participants are randomized to either control group receiving usual follow-up care, or to receive an intervention consisting of four group sessions three months post-surgery during which a modified version of the Stice dissonance-based intervention model is used. The sessions are held at the hospitals, and topics discussed are PA, eating behavior, social and intimate relationships. All participants are asked to complete questionnaires measuring HRQoL and other health-related behaviors and wear an accelerometer for seven days before surgery and at six months, one year and two years after surgery. The intention to treat and per protocol analysis will focus on differences between the intervention and control group from pre-surgery assessments to follow-up assessments at 24 months after RYGB. Patients’ baseline characteristics are presented in this protocol paper.

**Discussion:**

A total of 259 RYGB female patients has been enrolled in the “WELL-GBP”-trial, of which 156 women have been randomized to receive the intervention and 103 women to control group. The trial is conducted within a Swedish health care setting where female RYGB patients from diverse geographical areas are represented. Our results may, therefore, be representative for female RYGB patients in the country as a whole. If the intervention is effective, implementation within the Swedish health care system is possible within the near future.

**Trial registration:**

The trial was registered on February 23th 2015 with registration number ISRCTN16417174.

## Background

Obesity with its health-related co-morbidities is a major public health problem world-wide [1]. However, lifestyle interventions, such as dietary restriction and increased physical activity (PA), have limited effect on weight loss and maintenance [2, 3]. On the other hand, Roux-en-Y Gastric Bypass (RYGB) surgery results in marked and sustained weight loss as well as improvements in obesity-related comorbidities, compared with lifestyle interventions [4]. In 2014, laparoscopic RYGB accounted for more than 80% of all approximately 7000 bariatric procedures performed in Sweden, of which 75% were women [5]. With the increased use of laparoscopic sleeve gastrectomy, the proportion of laparoscopic RYGB decreased to 64% of the bariatric procedures performed in Sweden 2016 [6].

Weight regain and reoccurrence of obesity related comorbidities after RYGB are not uncommon [7, 8]. In most cases, this is not caused by surgical issues [9], but rather by difficulties with adaptations to the psychosocial life changes brought about by the procedure [10], or by the patient’s inability to adhere to the prescribed lifestyle recommendations [9]. Patient’s health-related quality of life (HRQoL) and body esteem tend to improve, and is closely associated with weight loss, following RYGB [11, 12]. The improvement in HRQoL typically peaks during the first year after surgery, when the weight loss is most rapid, and then declines as gradual weight regain starts to occur at one to six years after surgery [11]. It is easy to imagine a negative spiral experienced by RYGB patients as their weight loss slows down or weight is regained. Shame and stigmatization lead to increased sedentary behaviors and avoidance of PA, which in its turn might induce even greater problems with body esteem and weight regain. It is therefore important to create efficient preventive measures to avoid this vicious circle.

There is a growing interest in the role of PA and sedentary behavior in achieving optimal weight loss and improving health outcomes after RYGB [13]. Participation in moderate to vigorous intensity PA and reduced sedentary time play an important role in body weight regulation and may contribute to improvements of surgical outcomes after RYGB [14, 15]. In addition, achieving sufficient amounts of PA after surgery is of importance for long-term all-cause and cardiovascular mortality [16] as well as weight maintenance [17].

Although previous research suggests that dysfunctional eating behaviors, issues with body esteem and becoming habitually physically active represents a major challenge for many RYGB patients [10, 12, 18], few interventions to assist patients in meeting these challenges have been conducted. A 2015 systematic review and meta-analysis on interventions before and/or after bariatric surgery stated that the strength of evidence is limited by few trials, low methodological quality and short follow-up duration. The authors concluded that well-designed randomized controlled trials (RCTs) with at least two years follow-up are required. Previous RCTs evaluate weight-loss as the main outcome, with little focus on HRQoL and healthy levels of PA and sedentary behavior. This is of special concern as barriers to engage in PA and exercise, such as feeling too fat, is more common among obese adults [19]. In particular, RYGB patients frequently feel too overweight to exercise, or have fear of exercise-related injuries [15]. Hence, it may be appropriate to aim at reducing sedentary behavior after RYGB surgery, since reduced time spent sedentary may have beneficial effects on health and weight stability in populations with obesity, beyond the effects of light and moderate to vigorous PA (MVPA) [20, 21].

The need for an adequately powered RCT targeting patients undergoing bariatric surgery is justified for several reasons. Firstly, we are not aware of any theory-based counselling intervention for obese female patients after RYGB with appropriate statistical power. Secondly, as RYGB has been the most dominant bariatric procedure performed annually in Sweden during several years [6], it is timely to evaluate the effects of a novel theory-based post-bariatric intervention aimed at facilitating female patients’ psychosocial adjustment to daily life, including HRQoL, eating behavior, mood, body esteem, PA and sedentary behaviors. Such an intervention might also prevent further weight re-gain. Finally, a RCT is needed to evaluate the effects of an intervention, where the attainment of unbiased estimates is crucial and almost impossible to attain by observational studies.

The intervention framework was based on cognitive dissonance theory, which states that psychological distress is created when a person attempts to hold inconsistent sets of cognitions at the same time. People experience dissonance when they are encouraged to act in a way that is contrary to their cognitions, and they are prone to change their cognitions to create consistency [22]. People are also prone to change their future behavior to reduce dissonance [23]. In the current intervention, a modified version of Stice’s dissonance-based prevention model for eating disorders was adapted to RYGB patients. Apart from prevention of eating disorders, the model has been used for smoking cessation, prevention of unhealthy weight gain [24] and for promoting healthy PA behaviors [25].

### Aim

This paper presents the study design and methodology of the “WELL-GBP” intervention (wellbeing after gastric bypass) and describes the baseline characteristics of the participating women. The “WELL-GBP” trial is targeting female RYGB patients in a health care setting to improve HRQoL and health related behaviors after RYGB. The overreaching goal of the current study is to find ways of optimizing the outcome for the RYGB patient, not only in terms of maintained weight loss but also in terms of HRQoL, eating behavior, body esteem, social adjustment, PA and sedentary behavior. The specific aims of the “WELL-GBP” trial are to answer the following questions within a randomized controlled trial:What are the effects of a dissonance-based intervention on HRQoL (primary outcome), eating behavior, body esteem and social adjustment of female RYGB patients 24 months after surgery?What are the effects of a dissonance-based intervention on objectively measured levels of physical activity and sedentary behavior of female RYGB patients 24 months after surgery?

## Methods and design

This randomized controlled intervention study started in January 2015 in Sweden and is still ongoing: all baseline data has been collected and follow up measurements are going to be collected until end of 2019. The trial operates in three counties (Uppland, Närke and Södermanland counties), where participants are recruited from five hospitals: Uppsala University hospital, Danderyd hospital, St Görans hospital, Örebro University hospital and Ersta hospital. The trial has been approved by the Ethical Review Board Stockholm, Dnr 2013/1847–31/2. The trial has also been registered: ISRCTN16417174.

### Participants

As stated previously, approximately 75% of all bariatric surgery patients in Sweden are women [5]. To avoid lack of power associated with stratification of sex and limited number of male patients, we included only women in the current trial. Participants were recruited at each hospital approximately one to three months before RYGB surgery. The inclusion criteria were severe obesity (BMI ≥ 35 kg/m^2^), being able to understand and speak Swedish and the absence of any serious chronic disease such as stroke or myocardial infarction. All women who fulfilled the inclusion criteria and were accepted for primary RYGB surgery were asked to participate in the study. In general, patients are not eligible for surgery if they are under 18 years old, have not made previous serious attempts to lose weight or alcohol/substance abuse, recent heart disease or stroke or certain kinds of cancer, although the guidelines may to some extent differ between counties.

### Setting and recruitment

The study is conducted by Karolinska Institutet (KI) in collaboration with the five previously mentioned hospitals for recruitment. Altogether, the five hospitals account for approximately 25% of all bariatric surgery procedures performed in Sweden [6]. The recruitment procedure differed across the hospitals. At Uppsala University hospital and Örebro University hospital, the eligible RYGB patients were sent an information sheet together with a form for declaration of interest to participate in the study approximately three months before surgery. Thereafter the participants filled in the declaration of interest to the hospital, from which it was forwarded to KI. Ersta, Danderyd and St Görans hospitals had group information meetings, led by dietitians and specialized obesity nurses approximately one to three months before surgery. These group meetings occurred weekly and were visited by research staff from the current trial who informed patients about the trial and handed out declarations of interest forms for patients to fill in on-site. For all participants, research staff from KI then contacted the interested patients by telephone for consultation regarding participation in the study (*n* = 600). Participants were excluded if they failed to meet the inclusion criteria (*n* = 57), declined participation (*n* = 67), or if the research staff were unable to reach them by telephone, mail or e-mail (*n* = 73). The eligible participants received an accelerometer (Actigraph GT3X+) and questionnaires together with a form for informed consent, all sent by mail to their homes (*n* = 403). Once the participants sent back baseline assessments they were defined as a participant in the study (*n* = 304) (See Fig. 1). Participants who returned the baseline assessments received the results from their accelerometer measurement together with either a movie ticket voucher or a gift card (value 100 SEK) to promote participant retention. They received the same gift for all follow-up measures. Participant questionnaire were stored in numerical order in a secure and accessible place and manner. Data from questionnaires were entered manually twice by two different researchers to minimize bias. All personal data is handled in a confidential way according to KIs rules and the Swedish law.

**Fig. 1 Fig1:**
[figure not shown]
Flowchart of enrollment and randomization

Eligible participants who sent back the material (*n* = 304) were excluded from the study if they did not speak Swedish (*n* = 3), did not undergo the planned surgery (*n* = 9), changed their minds about wanting to participate (*n* = 2), died (*n* = 1), or if they underwent a sleeve gastrectomy instead of RYGB (*n* = 30) (see Fig. 1).

Participants were randomized to either intervention group (60%, *n* = 153) or control group (40%, *n* = 103) after surgery. Participants in the intervention group received a telephone call from the research staff approximately two months after RYGB where they obtained more detailed information about the group sessions. The dates for the four sessions were decided by the moderator in an attempt to fit the schedule of all group members. The control group participants were informed by mail.

### Pilot study

The first eight post-surgical patients at Ersta hospital in March and April 2015, were invited to participate in a pilot study (pilots are not included in the flow-chart). The aim was to test the intervention manual to see if it was understandable and acceptable for both the participants and the moderator. The participants provided feedback after each session, and small adjustments to the manual were made. The pilot intervention was conducted in June 2015 and five of the eight participants attended at least one of the sessions.

### Intervention description

The intervention started approximately two to three months after RYGB, and consisted of four group sessions during which a modified version of the Stice dissonance-based intervention model was used [24, 26]. See Table 1 for an overview of the intervention sessions. The sessions were offered once per week during four weeks, at the clinic where the women had surgery. Each session lasted for approximately 1,5 h and preferred group size was approximately five women per group. One of the research staff acted as a moderator and followed an intervention manual. As mentioned above, the intervention was based on the principle of cognitive dissonance theory [27] and the moderator encouraged the participants to talk to each other about how they wanted to act and behave to certain situations in the future, and in that way create the dissonance in relation to how they had been acting before their surgery. The group sessions aimed to provide the participants with strategies for coping with future difficulties with eating and PA behaviors, feelings of shame and other negative emotions, as well as to give them the opportunity to actively engage in thinking about their own and others’ current standpoints and perspectives in these areas. The sessions were not focused on teaching or informing the participants about appropriate eating or PA behaviors, but rather on eliciting active engagement and discussion and to take a stand on preferred ways of handling the discussed difficulties. Each of the four sessions focused on a different aspect of difficulties that might occur following RYGB. The manual for this project was developed by three researchers included in the development of the intervention, of whom two had previous experiences with RYGB patients, and one of whom is professor in clinical psychology.

**Table 1 Tab1:** Overview of the 4 intervention sessions in groups post RYGB Surgery

Topic for group sessions	Duration (mins)	Time after RYGB (weeks)	Content
1. Physical activity	90	12	-Sedentary behavior and motivation to minimize it -PA, how to avoid failure and make it a routine -How to overcome fears/difficulties with PA for RYGB patients
2. Eating Behaviors	90	13	-How to deal with cravings, powerlessness, feelings of emptiness and shame in relation to eating behavior -Different interpretations of health and appearance -Expectations and relation to food
3. Social relationships	90	14	How to handle different difficult social scenarios after RYGB, for example: -Comments from one’s surroundings about foods -Comments from one’s surroundings about weight loss -Eating at restaurants, buffets, parties
4. Intimate relationships	90	15	-Intimate and sexual relations, sexuality, avoidance and lust -Self-esteem and shame, how to improve it -Summarizing all sessions

The first session included PA and sedentary behavior. The participants were asked to suggest and discuss behaviors that may decrease sedentary behaviors throughout the day. For example, to think about what makes them not carry out planned PA, and to reflect on their own attitudes and approaches to PA. They were also asked to complete a home exercise, which entailed to write down what it meant for them to be physically active, what their long-term goal was in this area, how they were planning to realize their plans, what obstacles they expected to encounter, and how they would cope with them.

The second session addressed eating behavior and problems that are relatively common post- RYGB. The session focused on two (fictional) letters from women who had undergone RYGB two years earlier, and were now facing eating-related problems. The first woman reported extreme cravings for sweet, followed by uncontrolled eating, shame and feelings of loss of control. The second woman described a sense of loss and grief as she could no longer eat the types and amounts of food that she used to, including the foods she used to bake and cook for her family. Additionally, this session included expectations from the participants themselves and their surroundings, and different interpretations of health and appearance. The homework exercise was to write a reply to one of the letters, entailing support, understanding and suggestions for action that marked a clear stance toward the problem and obstacles.

The third session focused on social relations, including family, friends and colleagues. The participants were given the opportunity to reflect on and to role play different scenarios they often experienced themselves. For example, people around them tried to get them to eat foods that are unsuitable after RYGB, gave unhelpful comments or criticisms, or they found themselves at a restaurant with big portions and/or lack of suitable menu options. As a homework exercise each participant wrote a letter to herself to be sent back to her after six months, containing overall goals, mindset and strategies and at least one “lesson learned” from the group sessions.

The fourth session dealt with intimate relations and sexuality. The participants were asked to reflect on and to discuss possible expectations, from themselves and from their partners, as well issues related to lack of a partner, which might arise after surgery. In addition to this, this session also included (fictional) letters. These might have to do with experiencing or not experiencing sexual desire, feelings about one’s own body following major weight loss, and to deal with desired or unwanted sexual attention from others.

During the four sessions, the majority of participants expressed a desire to have more group meetings approximately one year after the surgery, since they felt they wanted to discuss problems and strategies when they had recovered and started to get into their new habits post-surgery. Therefore, a booster session was added and was held approximately one year after surgery. The booster session was a compilation of the four previous sessions. The participants were asked to reflect on the previous topics: PA, eating behavior, social relations and intimate relations and sexuality for approximately ten minutes per topic. Lastly, participants were encouraged to share the experience of receiving the letter six months after they had written it to themselves and to further reflect on experienced problems and possible resolutions after surgery. To the best of our knowledge, none of the participants included in the “WELL-RYGB” Intervention study have suffered any adverse effects so far.

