### Power calculations

Power calculations showed that 95 participants were needed in each group to attain a statistical power of at least 0.80 (based on HRQoL as the primary outcome), with an expected moderate effect size (Cohen’s d = 50), and alpha set at 0.05. Based on previous similar studies [25, 40], we expect 20% drop-out of patients during two years of follow-up. Thus, a minimum of 240 patients was required, and at final total of 259 participants were recruited and randomized either to the intervention (60%) or to usual care (40%).

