### Statistical analyses

The statistical analyses will focus on differences between the intervention and the control group from pre-surgery assessment to follow-up assessments at 24 months after RYGB. The women’s changes in weight will be taken into account in the analysis by stratification or adjustment. Primary analysis will be intention to treat analysis, including women who attended at least one session (*n* = 103). We will also conduct per protocol analysis including the women who have attended all four sessions (*n* = 33). We will also perform sensitivity analysis in order to detect any possible dose-response effects such as if the main outcomes will differ depending on if a woman have attended one, two three or all four sessions. Furthermore, individual factors, e.g. patient beliefs about causality of obesity, and contextual factors, e.g. variations in implementation of the intervention between centers for bariatric surgery, might moderate the effect of the intervention on health outcomes. These issues will be analyzed by mixed linear regression models or generalized estimation equations (GEE) to analyze repeated measurements over time. [41].

For the assessments of the baseline characteristics for the intervention and control group presented in this protocol, the analysis have been separated into women randomized to intervention group and women randomized to control. X^2^-tests were performed for categorical variables and t-tests for continuous variables, and because the majority of the continuous variables were not linear distributed, the Kruskal-Wallis test was used.

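### Women in the intervention arm are treated in discussion groups of about five, but the stated model names no session-group term, so its standard errors would be somewhat too small

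*Protocol article*

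**What the plan says.** **Delivery.** The Intervention description section sets out four weekly sessions of about 1.5 hours, led by one moderator from the research staff working from a manual; the "preferred group size was approximately five women per group". The sessions are not meant to teach. The women are to discuss with each other, and that exchange is how the dissonance is meant to arise. A booster session was added at about one year. Controls receive usual follow-up care (Measurements section), with no study groups.

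**Analysis.** The Statistical analyses section names mixed linear regression or GEE "to analyze repeated measurements over time". Differences in implementation between centres appear as a possible moderator. Session group is not mentioned.

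**Sample size.** The Power calculations section says "95 participants were needed in each group to attain a statistical power of at least 0.80", "with an expected moderate effect size (Cohen’s d = 50", with "alpha set at 0.05". It adds "we expect 20% drop-out of patients during two years of follow-up" and concludes that "a minimum of 240 patients was required". It mentions no ICC, group size or design effect.

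**The concern.** Women in one session group share a moderator, four sessions and, above all, each other's contributions, which are the active ingredient. If this makes their 24-month outcomes more alike than those of women in different groups, the mean of the intervention arm is less precise than the number of women suggests. Controls have no such structure, so the design is partially nested: clustered in one arm only.

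A model that allows for correlation between one woman's repeated measurements, but not between women in the same group, understates the variance of the intervention mean. Confidence intervals are then too narrow and a nominal 5% test rejects too often under the null hypothesis. A larger sample with the same group size does not cure this, so spare power is no protection.

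**Working it through.** **Inputs from the protocol article.** Group size about 5, intervention arm only (Intervention description). Randomised: 156 and 103 (Baseline data; the intervention number is given differently elsewhere). Attended at least one session: 103; never attended: 53 (Discussion). Expected drop-out 20%; 95 per group; alpha 0.05, taken as two-sided; d printed as 50 and read as 0.50 because it is called moderate (Power calculations).

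**Assumed.** ICC 0.05, 0.10 and 0.15, because the article gives none.

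**Step 1: the plan's own figures.** n per arm = 2 × ((1.96 + 0.842)/0.50)² = 62.8, so 63, not 95. With 95 per arm the power at d = 0.50 is 0.93. The drop-out step does reproduce: 190/0.80 = 237.5, so 238, against 240 stated. That 95 does not follow from the stated inputs is a separate matter.

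**Step 2: power with clustering.** Design effect DE = 1 + (m − 1) × ICC, applied to the intervention arm only. SE = √(DE/n₁ + 1/n₀) in SD units. Power = Φ(0.50/SE − 1.96). With m = 5 and 95 per arm:

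| ICC | DE | SE | Power |
|---|---|---|---|
| 0 | 1.00 | 0.1451 | 0.93 |
| 0.05 | 1.20 | 0.1522 | 0.91 |
| 0.10 | 1.40 | 0.1589 | 0.88 |
| 0.15 | 1.60 | 0.1654 | 0.86 |

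Power reaches 0.80 at DE = 2.026, which is an ICC of (2.026 − 1)/4 = 0.26.

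**Step 3: type I error, attenders against controls.** 103 × 0.80 = 82 per arm. The ratio of true to naive SE is √[(DE/n₁ + 1/n₀)/(1/n₁ + 1/n₀)], which for equal arms is √((DE + 1)/2). Type I error = 2 × [1 − Φ(1.96/ratio)]. Since 20% drop-out turns five attenders into four analysed, m = 4 is the consistent case and m = 5 an upper one.

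| ICC | m = 4: ratio | m = 4: error | m = 5: ratio | m = 5: error |
|---|---|---|---|---|
| 0.05 | 1.037 | 5.9% | 1.049 | 6.2% |
| 0.10 | 1.072 | 6.8% | 1.095 | 7.4% |
| 0.15 | 1.107 | 7.7% | 1.140 | 8.6% |

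**Step 4: type I error, all randomised women.** 156 × 0.80 = 125 against 82. About 82 of the 125 attended and are clustered; the other 43 never attended and are singletons. The average design effect is (82 × DE + 43)/125. For m = 4 and ICC 0.05 this is (82 × 1.15 + 43)/125 = 1.098, with ratio 1.019 and error about 5.4%. For m = 5 and ICC 0.15 it is (82 × 1.60 + 43)/125 = 1.394, with ratio 1.075 and error 6.8%. Treating all 125 as grouped in fives would give 5.9-7.8%, which is too high because it clusters women who never came.

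**The case against.** **Power.** A reader might infer that the power is overstated. The documents do not support this. The plan claims only 0.80 or more, and at d = 0.50 that holds with 95 per arm up to an ICC of about 0.26. Even 82 per arm with five per group gives 0.86, 0.83 and 0.80 at the three assumed ICCs. If the 95 really rested on d of about 0.41, power would fall to 0.76 at ICC 0.05 and 0.73 at ICC 0.10, but the article does not say so. Power is lower than under independence, and no more than that can be said.

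**The model.** A reader might also say that the plan treats all women as independent. It does not say this. Mixed models and GEE can both carry a group level, the article is condensed, and a random-effects structure can sit in an analysis plan that is not shown. This stands in part: it makes the point a request to name the term rather than proof of a wrong analysis. But the article does give the correlation its models are meant for, and session group is not it.

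**Size.** The ICC is assumed throughout. The outcome is measured about 20 months after the weekly sessions, the article does not say whether the same groups met again for the booster, and only 33 women attended all four sessions. If about five were invited per group, 66% attendance and 20% drop-out leave 5 × 0.66 × 0.80 = 2.6 analysed per group. For 82 against 82 the error is then about 5.5% at ICC 0.05 and 5.9% at ICC 0.10. Nothing in the article favours the upper end of the range. This stands and limits the size, not the direction.

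**Conclusion.** The concern holds as a moderate one about the analysis. The intervention works through interactive groups in one arm, and the model as described has no session-group term, so for any positive group correlation its standard errors are too small. With ICC 0.05-0.15 the true type I error is about 5.9-7.7% for 82 against 82 with four per group, at most 6.2-8.6% with five, and about 5.4-6.8% for 125 against 82 with never-attenders ungrouped. These figures rest on an assumed ICC, equal group sizes and normal approximations. The sample-size claim is not contradicted. This is a cheap improvement, not a flaw that undermines the trial.

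**What to change.** Before the 24-month analysis, add to the primary mixed model a random session-group effect that applies to the intervention arm only. Each control, and each intervention woman who never attended, is her own cluster. Use Satterthwaite or Kenward-Roger degrees of freedom, because the groups are few: 103 attenders in fives make about 21. Report the estimated ICC.

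This needs each attender's session group. The article does not say that group membership was recorded. Sessions were scheduled by group and attendance was counted, so scheduling or attendance records may supply it, and the sponsor should confirm that they do.

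The cost is one model term, the retrieval of group membership and slightly wider intervals. At ICC 0.05 the true standard error is about 2-5% above the naive one in the cases worked here.
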